## 9.0 STUDY PROCEDURES

### 9.1 Schedule of Events

Table 1: Schedule of Events

|                                                                           | Screening
(Day 0) | Visit 0
Day 1
(±14d) | Home
Specimen*1
Day 14 | Visit 1
Day 30
(±7d) | Home
Specimen*2
Day 44 | Visit 2
Day 60
(±7d) | Home
Specimen*3
Day 74 | Visit 3
Day 90
(±7 d) | Home
Specimen*4
Day 104 | Visit 4
Day 120
(±7 d) |
|---------------------------------------------------------------------------|----------------------|-----------------------------------|------------------------------|-----------------------------------|------------------------------|-----------------------------------|------------------------------|------------------------------------|-------------------------------|-------------------------------------|
| Visit format: Remote                                               |                      |                                   |                              |                                   |                              |                                   |                              |                                    |                               |                                     |
| Information video                                                         | X                    |                                   |                              |                                   |                              |                                   |                              |                                    |                               |                                     |
| Self-eligibility assessment                                               | X                    |                                   |                              |                                   |                              |                                   |                              |                                    |                               |                                     |
| Visit format: In person                                            |                      |                                   |                              |                                   |                              |                                   |                              |                                    |                               |                                     |
| Informed consent: individual written consent                              |                      | X                                 |                              |                                   |                              |                                   |                              |                                    |                               |                                     |
| Randomization                                                             |                      | X                                 |                              |                                   |                              |                                   |                              |                                    |                               |                                     |
| Dispensation of study drug                                                |                      | X                                 |                              | X                                 |                              | X                                 |                              | X                                  |                               |                                     |
| Interview by study staff                                                  |                      | X                                 |                              | X                                 |                              | X                                 |                              | X                                  |                               | X                                   |
| Adverse event assessment                                                  |                      |                                   |                              | X                                 |                              | X                                 |                              | X                                  |                               | X                                   |
| Self-collected viral detection sample*                                    |                      | X                                 | X                            | X                                 | X                            | X                                 | X                            | X                                  | X                             | X                                   |
| Blood for laboratory outcomes                                             |                      | X                                 |                              | X                                 |                              | X                                 |                              | X                                  |                               | X                                   |
| Urine for pregnancy tests (female participants of reproductive potential) |                      | X                                 |                              | X                                 |                              | X                                 |                              | X                                  |                               |                                     |

|                                         |  |     |   |   |   |   |   |   |   |   |
|-----------------------------------------|--|-----|---|---|---|---|---|---|---|---|
| Evaluation of QT interval               |  | X^^ |   | X |   | X |   | X |   | X |
| Return Home Specimen                    |  |     |   |   |   |   |   |   |   | X |
| Visit Format: Remote             |  |     |   |   |   |   |   |   |   |   |
| Baseline questionnaire                  |  | X   |   |   |   |   |   |   |   |   |
| Weekly visit-specific questionnaire**** |  | X   |   | X |   | X |   | X |   | X |
| Home specimen reminder**                |  |     | X |   | X |   | X |   | X |   |
| Short-term psychological assessment***  |  | X   |   |   |   | X |   |   |   | X |
| Unscheduled visits^                     |  | X   |   | X |   | X |   | X |   | X |

\* Depending on availability of viral detection samples supplies, this will be either be a swab (defined in section 8.2.2) or saliva.

\*\* Weekly short electronic questionnaire will be emailed to participants: including new or pending confirmation of COVID-19 results, clinical outcomes of COVID-19, days unable/ineligible to work due to COVID-19 and adherence.

\*\*\* An electronic message will be emailed to participants reminding them to collect their viral sample. The email will prompt them to acknowledge that the sample had been collected.

\*\*\*\* These assessment tools will be sent to participants via email to be answered remotely.

^ Study coordinators will be available for unscheduled visits remotely if participants have concerns, problems with study drug, procedures.

^^. This will include either a baseline ECG conducted at the time of enrolment, or review of a resting ECG done within the past 3 months.

## Special Schedule Considerations:

**If any participant is under quarantine for suspected COVID-19 (ie they are awaiting confirmatory testing results) and, therefore, unable to make a study visit in a visit window,** a remote visit will occur and every effort will be made to have an in-person study visit scheduled as soon as they are cleared as negative for COVID-19 for sample collection.

**If any participant is confirmed COVID-19 positive during the study, the above scheduled visits will continue *remotely* (telephone) and the weekly email questionnaire will continue.** During the time in which they are symptomatic and under isolation, the following events will be suspended: dispensation of drug, self-collected viral detection sample, venous blood draw. COVID-19 positive participants who have recovered and have been deemed safe to return to work by their institution will be asked to return to the above study schedule.

**COVID-19 positive participants who have been deemed safe to return to work will be given the option of either a) resuming their blinded study drug and then entering the open-label extension at day 90 as previously scheduled, or b) starting the 30-day open-label extension immediately.** The rationale for providing the option to resume blinded study drug is that it remains unknown whether individuals who recover from COVID-19 infection remain susceptible to re-infection, and acquiring COVID-19 does not necessarily mean that the blinded study drug that the participant had been using was not providing partial protection. The rationale for providing the option to skip immediately to the open-label extension is that some participants may understandably prefer to abandon their study drug under these circumstances, and the study has committed to providing every participant with a one-month open-label extension.

### 9.2 Information and Eligibility Session: (Day 0) - Conducted remotely

Healthcare workers from the participating sites will be invited via email to view an online informational video in which study information, regarding the informed consent document and eligibility criteria will be provided and reviewed. This private YouTube video will not be searchable from within YouTube nor via external search engines (ex. Google). It will only be accessible by the link that will be emailed to hospital employees via their hospital email address. The Department Heads, supervisors, and other persons with authority over the potential participants will not be given access to any information regarding who has or has not accessed the video, or who is or is participating in the study. Access to this informational video will be available to potential participants at UHN and all other

participating sites (SHS, SMH, SHSC) who have been issued the link. The email containing the link to the informational video will also include a Study Fact Sheet as an attachment. Viewing the video or reviewing the Study Fact Sheet does NOT replace written informed consent (see Section 9.3). This approach to the informed consent process is congruent with current physical distancing practices in the case of a public health emergency during COVID-19. Participants willing and who self-screen as eligible will be able to have an individual appointment with study coordinators within 14 days of viewing the informational video in order to undergo the formal eligibility screening and consent process.

### 9.3 Baseline Visit: (Day 1) Conducted in-person

Participants willing and who self-screen to be potentially eligible will be asked to attend individual appointments with study coordinators within 14 days of information sessions. These baseline visits will be conducted over consecutive days and will allow participants to ask questions about participation and allow the study staff to provide, review and obtain the informed written consent, assess for eligibility, and obtain multiple forms of contact information. All WOCP will have a screening urine pregnancy test for eligibility and all participants will have a baseline QTc interval reviewed and recorded. Written informed consent will be obtained before any study specific activities occur.

Participants who are enrolled at this point will complete the baseline study visit which will include:

- **Randomization and dispensing study drug:** The coordinator must confirm receipt of the package with the participant, and review dosing.
- **Interview:** The coordinator should obtain information from participants to complete the baseline medical history and concomitant medication assessment.
- **Baseline resting ECG:** The coordinator will review a baseline resting ECG and record the QTc interval.
- **Online Questionnaire instructions:** The coordinator should explain to the participant how to access and complete the online questionnaire that will be sent to them via email weekly.
- **Self-collected viral detection sample:** The coordinator should review the printed instructions on how to self-collect, label, date and package the viral detection sample. The participant should then collect and date the sample and package it.
- **Blood for serology and other laboratory markers:** The coordinator should collect one tube of blood (10ml EDTA).
- **Baseline questionnaire:** will be emailed to participant to complete at day 1 (see Questionnaire Content document submitted)

- **Psychological distress questionnaire:** will be emailed to participant to complete at day 1.

#### 9.4 Study Visits 1-4 (Follow-up at Day 30, 60, 90, and 120): Conducted in person.

Participants will be schedule for monthly Study Visit appointments. These are expected to take a maximum of 30 minutes, and in many cases much less. Whenever possible, the study visits will be coordinated with the participant's scheduled ED shift in order to minimize travel and burden on the participant. The components of the Study Visit are as follows:

- **Interview:** The coordinator will review the participant's COVID-19 symptom reporting, their responses to the Adverse Events Questionnaire and Tolerability Questionnaire. The research coordinator will review the responses prior to releasing the next installment of study drug/placebo. If the participant has any concern regarding adverse events or other aspect of the study, they will have the opportunity to discuss these with the research coordinator during the visit.
- **Urine pregnancy test:** for women of childbearing potential.
- **Self-collected viral detection sample:** As above.
- **Blood for serology and other laboratory markers:** As above.
- **QTc interval evaluation:** The QTc will be measured and recorded.
- **Dispense study drug:** The coordinator must confirm receipt of the package with the participant, and review dosing.
- **Psychological distress questionnaire:** will be emailed to participant to complete at day 60 and day 120.

Participants with confirmed COVID-19 will be asked to discontinue their study tablets (see Section 6.7). They will not present for in person visits until they are cleared to return to work.

#### 9.5 Weekly virtual questionnaire (Day 7 to day 120): Conducted remotely

Questionnaires will be administered weekly electronically through REDCap, which will be emailed to participants directly. Self-reported questionnaires will include ascertaining COVID-19 testing underway or completed (with results), adherence scales, and for participants with confirmed COVID-19, questions will also include symptom duration, time off work and hospitalization. An email reminder will be sent for each questionnaire.

## 9.6 Every Two-Weekly Viral Detection Sample Collection

Participants will be screened for the presence of SARS-CoV-2 every two weeks by the methods described in Section 8.2.2. On the weeks that correspond to the monthly Study Visit, this collection will occur during the Study Visit. During the intervening weeks, participants will self-collect the sample at home and store them in a biosafety bag in their freezer. They will receive an email reminder to collect the sample on these weeks. The participant will return the sample to the study coordinators at their next monthly.

## 9.7 Early Termination Visit

If a participant chooses to withdraw from the study prematurely after the baseline visit but before the study end, efforts should be made to complete all study activities at the next closest study visit. Participants who discontinue study drug prematurely but consent to still be followed up in the study should follow routine protocol-defined procedures.

## 9.8 Re-contact of Participants after Trial Termination

Participants will be consented to be re-contacted after trial termination for participation in follow-up studies.

# 10.0 EVALUATION and REPORTING OF ADVERSE EVENTS

## 10.1 Adverse Event Reporting

Toxicities will be graded on a 4-point scale according to standard guidelines outlined in the “Division of AIDS Table for Grading the Severity of Adult and Pediatric Adverse Events”. In general, grade 1 and 2 events will not be considered adverse events, but details should be documented in the source documents. Stable chronic conditions which are present prior to clinical study entry and do not worsen are not considered adverse events and will be accounted for in the participant’s medical history. Participants who have an adverse event (AE) should be followed and treated by the site Investigator until the abnormal parameter or symptom has resolved or stabilized. It is up to the clinician to determine that the AE is either resolved or that it has reached a stable state, after which no further follow-up is necessary. There should also be source documentation to support this determination.

At each contact with the participant, information regarding adverse events will be elicited by appropriate questioning and examinations, and will be recorded immediately on a source document (e.g., progress notes, laboratory reports, survey tools, and data collection tools). The start date, stop date, severity of each reportable event, and the PI's judgment of the AE's relationship to the study medication/intervention will also be recorded.

The Investigator or designee must report any severe adverse event (SAE) occurring in a participant receiving study drug to the Sponsor within 24 hours, even if the SAE is not drug-related. This should be done by telephone and by sending a faxed or emailed copy of the Serious Adverse Event form plus other supporting documentation, as required. All additional follow-up evaluations must also be reported as soon as possible in the same manner. All SAEs will be followed until the Investigator agrees that the event is satisfactorily resolved, becomes chronic, or that no further follow-up is required.

A Serious Adverse Event is defined as an AE meeting one of the following:

- Death during the period of protocol-defined surveillance
- Life Threatening Event (immediate risk of death at the time of the event)
- In-patient hospitalization or prolongation of existing hospitalization during the period of protocol-defined surveillance
- Results in congenital anomaly or birth defect
- Results in a persistent or significant disability/incapacity
- Any other important medical event that may not result in one of the above outcomes may

The intensity (severity) of each adverse/serious event will be graded according to the toxicity table and toxicity guidelines provided by the DAIDS Table for Grading the Severity of Adult and Pediatric Adverse Events. The DAIDS Table will be provided with the Operations Manual.

All SAEs which occur during the course of the study must be reported to the site Project Manager within 24 hours of the site becoming aware of the event. The Project Manager will be responsible for reporting SAEs to Health Canada on behalf of the Sponsor-Investigator.

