### **Secondary outcomes measures are:**

- a) **Adverse events:** as defined using the DAIDS Table for Grading the Severity of Adverse Events, until day 120^27
- b) **Symptom duration of COVID-19:** measured in days.
- c) **Days of hospitalization attributable to COVID-19:** The number of days (or partial days) spent admitted to an acute care hospital during the study period.

- d) **Respiratory failure requiring ventilatory support attributable to COVID-19:** The number of days (or partial days) requiring i) non-invasive and ii) endotracheal intubation with ventilation during the study period.
- e) **Mortality** attributable to COVID-19 and all-cause mortality during the study period.
- f) **Number of days ineligible/unable to work due to COVID-19:** measured from symptom onset to return to work date.
- g) **Seropositivity:** reactive serology by day 120.
- h) **Short-term psychological impact of exposure to COVID-19** will be measured at the beginning of randomization (day 1), during the randomized period (day 60) and during the open-label period (day 120) using the K10, a validated measure of non-specific psychological distress, with a standard cutoff score of  $\geq 16$ .

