#### 6.1.2 Expected Side Effects:

Most side effects are seen in treatment doses and in long term use (over years). Most are reversible with stopping the medication (unless otherwise indicated):

**Very Common: (>10%):** Abdominal pain, nausea

**Common: (1-10%):** Blurring of vision due to a disturbance of accommodation, diarrhea, vomiting, anorexia, headache, affect lability, skin rash/pruritis,

**Uncommon: <1%:** Vertigo, tinnitus, maculopathies (in early form is reversible), abnormal liver function tests, dizziness, nervousness, pigmentary changes in skin, hair

**Not known (event rate):** blood disorders, cardiomyopathy, prolonged QTC, urticaria, angioedema, bronchospasm, myopathy

**Serious:** Most serious toxicities are associated with long term use (ie. over years) and include: retinopathy, liver dysfunction, and hemolysis in G6PD deficient patients (NB: Product monograph suggests G6PD testing prior to initiation but post-marketing studies suggest risk is low and in standard clinical practice this is not done.)

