### 11.3.2 Analysis of Secondary Outcome Measures

**Adverse events** will be tabulated by study arm. The percentages of participants experiencing each type of AE, or any AE will be calculated by severity level. The rate per 100 person-days will also be calculated by AE and severity level. If warranted, AEs will be compared between groups using the methods for the primary analysis. **Symptom duration, duration of hospitalization due to COVID-19 disease, days of respiratory failure requiring ventilatory support attributable, and number of days ineligible/unable to work due to COVID-19** will be summarized within group by the median and interquartile range as well as the mean. As the majority of participants will have zero for all of these outcomes, a bootstrap hypothesis test, with stratification by site, will be used to test the hypothesis of no treatment effect. A 95% confidence interval for the mean difference in days will also be computed using the bootstrap. Mortality is expected to be very low, so will simply be summarized by a count and percentage in each arm. The relative risk of mortality by 90 days will be calculated if feasible. **Seropositivity** will be analyzed by the same approach described for the primary outcome. **Short-term psychological impact of exposure to COVID-19** as measured by the K10 will be summarized by group at each of the three time points (day 1, 60, and 120), using the mean and standard deviation as well as the percentages with scores at or above the standard cutoff score of 16. As the trial is blinded, there is no expectation of a direct effect of treatment on the K10. Those who become infected may have higher scores, so results will also be presented according to the previous occurrence of an infection. The primary comparison of this outcome will use a linear model to estimate the effect on 60-day values of site, study arm, and job class, using the day 1 value as a covariate. The relative risks of exceeding the threshold at 60 days for these same variables will be estimated in a log-binomial model with the same covariate. The change in K10 between days 60 and 120

will be estimated to assess whether there is a reduction in psychological impact once participants know they are on prophylaxis with an active drug.

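### Section 10.1 generally takes grade 1 and 2 events out of the adverse-event definition, in conflict with the adverse-event outcome in 2.4 and its analysis by severity in 11.3.2

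*Protocol*

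**What the plan says.** Section 10.1 first sets the scale: "Toxicities will be graded on a 4-point scale according to standard guidelines". It then sets the lower half of that scale aside: "In general, grade 1 and 2 events will not be considered adverse events, but details should be documented in the source documents". Later in the same section, the details to be recorded are tied to a narrower class of event: "The start date, stop date, severity of each reportable event", together with the judged relationship to study drug.

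Section 2.4 lists adverse events as secondary outcome (a), "as defined using the DAIDS Table for Grading the Severity of Adverse Events, until day 120". It gives no minimum grade.

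Section 11.3.2 says how the outcome will be summarised: "The percentages of participants experiencing each type of AE, or any AE will be calculated by severity level". It adds: "The rate per 100 person-days will also be calculated by AE and severity level". A comparison between arms is conditional there: it is made only if thought warranted, by the method used for the primary analysis.

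Section 6.1.2 puts "Abdominal pain, nausea" in the class above 10%. Headache, rash, vomiting and diarrhea are among the effects at 1-10%. On severe harm it says: "Most serious toxicities are associated with long term use". Randomized treatment lasts 90 days, followed by a one-month open-label period.

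**The concern.** The three sections give different answers to one question: which grades count as an adverse event in this trial? Sections 2.4 and 11.3.2 read as if all four do. Section 10.1 says that, in general, only two do.

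The participants are health care workers taking a preventive drug, and section 1.3 says that it may bring them no medical benefit. Tolerability is therefore a large part of the evidence on whether the drug could be used, and the randomized, blinded comparison of adverse events is the natural source for it. If events below grade 3 are not adverse events, that comparison rests on the events expected to be rarest over three to four months and passes over those the protocol expects to be common. A small difference between arms could then reflect the definition and not the drug.

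The qualifier in 10.1 adds a second problem. Each of the five sites may decide that a particular grade 1 or 2 event does count, and no criterion is given. Counts could then differ between sites for reasons unrelated to treatment.

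**Working it through.** The protocol states no figure on this point, so there is none to reproduce. The check is a comparison of sections, followed by an illustration of scale.

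**Comparison of sections**

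1. *Definition.* 10.1 uses four grades and generally excludes grades 1 and 2. What remains is grades 3 and 4, plus whatever a site chooses to include.
2. *Outcome.* 2.4(a) relies on the DAIDS grading table with no cut-off. This does not agree with step 1.
3. *Analysis.* 11.3.2 reports each type of event, any event, and rates per 100 person-days, by severity level. Under step 1 the two lower severity levels are generally empty, and the any-event row becomes roughly any grade 3-4 event.
4. *Data.* 10.1 asks for start date, stop date and severity for reportable events. If grade 1-2 events are not reportable, the fields needed to tabulate them by grade and date are not required. A later analysis plan could not count on having them.
5. *Possible repair elsewhere.* 8.1 has the coordinator document all side effects and the study physician assess severity and relationship. 9.4 has adverse-event and tolerability questionnaires reviewed at visits. Neither section assigns that information to outcome (a) or to the tables in 11.3.2.

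**Illustration of scale**

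From the protocol: 988 participants (3.1) allocated 1:1 (5.1), so 988 / 2 = 494 per arm.

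Assumed, and not in the protocol:
- a given gastrointestinal event occurs in 10% of the hydroxychloroquine arm and 5% of the placebo arm, all grades counted;
- a share f of these events is grade 1-2, the same in both arms;
- the test is a two-sided 5% comparison of two proportions.

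With grades 1-2 excluded, the countable proportions are p1 = 0.10(1 − f) and p2 = 0.05(1 − f). With p̄ = (p1 + p2)/2 and n = 494,

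power = Φ{ [p1 − p2 − 1.96·√(2p̄(1 − p̄)/n)] / √([p1(1 − p1) + p2(1 − p2)]/n) }.

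For f = 0, p̄ = 0.075. The pooled standard error is √(0.13875/494) = 0.01676 and the unpooled one is √(0.1375/494) = 0.01668. Then (0.05 − 1.96 × 0.01676)/0.01668 = 1.03, and Φ(1.03) is about 0.85.

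| Share at grade 1-2 (assumed) | p1 vs p2 | Expected participants, 494 × p | Power |
|---|---|---|---|
| 0% excluded (all grades counted) | 10% vs 5% | 49 vs 25 | 85% |
| 50% | 5% vs 2.5% | 25 vs 12 | 54% |
| 80% | 2% vs 1% | 10 vs 5 | 25% |
| 90% | 1% vs 0.5% | 5 vs 2.5 | 15% |
| 95% | 0.5% vs 0.25% | 2.5 vs 1.2 | 9% |

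The ratio between arms is 2 in every row. Only the number of countable events changes.

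**The case against.** The best defence is that the sentence in 10.1 sits in a section on reporting and opens with a qualifier. It can be read as a threshold for handling and reporting, with 2.4 and 11.3.2 left to govern the analysis; the reference to reportable events fits that reading. It is a possible intention, but the sentence says what counts as an adverse event, not what must be reported, and no other section says that the outcome uses a wider definition. The defence shows that the text is ambiguous. It does not remove the conflict.

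A second defence is that the information is kept. This stands in part. Grade 1-2 details go into source documents, and side effects are elicited at the monthly visits. A reader might infer that these events vanish from the trial, and the protocol does not support that. What is missing is any route from the source documents to the adverse-event outcome.

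A reader might also infer that most of hydroxychloroquine's side effects are excluded, or that the trial would report almost no difference in adverse events. Neither can be stated as fact. The protocol gives frequencies but no grades and no placebo rate, and 6.1.2 says that most side effects are seen at treatment doses and with use over years, so its percentages may not carry over to 90 days of prophylaxis. A near-absent difference would need the strict reading of 10.1, a high share of grade 1-2 events and the assumed rates all at once.

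Finally, adverse events are not a powered endpoint, and any comparison would use the primary-analysis method, a Cox model, and not a test of two proportions. That stands. The power figures show how quickly information is lost; they do not describe a planned test.

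**Conclusion.** The point holds as a conflict within the protocol. Sections 10.1, 2.4 and 11.3.2 do not agree on which grades enter the adverse-event outcome. If 10.1 is followed as written, the comparison is generally confined to grades 3 and 4, subject to site discretion. It would then omit many of the effects listed in 6.1.2, to the extent that they are grade 1-2. That they mostly are is a reasonable expectation, because the protocol calls most of them reversible and links most serious toxicity to use over years, but it is an inference.

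The size cannot be fixed from the protocol. Under the assumed 10% versus 5%, the loss runs from moderate (85% to 54% power at a half share of grade 1-2 events) to nearly complete (9% at a 95% share). The defect bears on the harm comparison only and leaves the primary outcome, the 92 required events and the sample size of 988 untouched. It is a stated rule that other sections contradict, not a detail left for a later analysis plan, and it decides which data are required.

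**What to change.** Reconcile 10.1 with 2.4 and 11.3.2. Either delete the sentence on grades 1 and 2, or reword it so that it covers only reporting and handling and plainly does not define the outcome. Then state that every new or worsening event of grade 1 to 4 is entered in the database with start and stop dates, grade and judged relationship to study drug, and is tabulated by grade and arm under 11.3.2. Extend the list of required fields in 10.1 from reportable events to all such events. If workload is a concern, expedited reporting and detailed narratives can stay limited to grade 3 and above and serious events.

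The cost is somewhat more data entry. Side effects are already elicited and documented at the monthly visits under 8.1, so no new visit or procedure is needed. Because the synopsis gives the trial as recruiting, grade 1-2 events already noted in source documents would also need to be entered, as far as their dates and grades were recorded.
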